## Abstract

**Introduction:**

The use of invasive life support in patients with a prolonged critical illness clearly saves lives but carries substantial risks, including intensive care unit-acquired weakness (ICUAW) and long-term disability. Early mobilisation might improve outcomes, yet the evidence is conflicting and complicated by the lack of a responsive outcome measurement to detect change in critically ill patients’ physical function and activity. The Chelsea Critical Care Physical Assessment tool (CPAx) is a valid and reliable instrument for patients at risk of ICUAW. However, its ability to measure change over time (responsiveness) and the minimal clinically important difference (MCID) have not yet been rigorously investigated.

**Methods and analysis:**

The primary objective of this prospective, international, multicentre, longitudinal cohort study is to investigate responsiveness and to establish the MCID of the CPAx during the ‘intensive care unit (ICU) period’, from ICU baseline to ICU discharge, and ‘hospital period’, from ICU to hospital discharge. Adults with any critical illness who are mechanically ventilated for at least 72 hours, expected to remain in ICU (≥48 hours) and being treated by a physiotherapist are eligible for study inclusion. Functional measurements, including the CPAx and a global rating of change (GRC) scale, will be collected during routine physiotherapy. Responsiveness will be evaluated primarily using the GRC as an anchor to distinguish changed from unchanged/deteriorated patients (criterion validity). As such, the magnitude of change will be analysed with receiver operating characteristics. Additionally, construct validity will be explored with correlation coefficients and effect sizes to confirm/reject a priori formulated hypotheses. MCID will be investigated with anchor-based and distribution-based methods. We plan to recruit 120 patients across three sites in Australia and Switzerland.

**Ethics and dissemination:**

Ethical approval has been obtained from each local ethics committee (Canton of Bern, Switzerland (2024-00346), Monash Health, Australia (HREC/106143/MonH-2024-438474(v3)), the Alfred, Australia (490/24)). The results will be disseminated through international/national conferences, peer-reviewed journals and social media. The high quality, rigorous testing of the CPAx could benefit researchers, clinicians and patients.

**Trial registration number:**

NCT06419699.

STRENGTHS AND LIMITATIONS OF THIS STUDYRigorous COnsensus-based Standards for the selection of health Measurement INstruments (COSMIN) methodology is applied to investigate the Chelsea Critical Care Physical Assessment tool in a large, international, multicentre cohort of critically ill adults with a prolonged intensive care unit (ICU) stay.Responsiveness and minimal clinically important difference are obtained for two clinically relevant, patient-centred periods, but major functional changes are conceivable in between.The burden for patients is kept minimal by using data from routine care.Change is estimated by clinicians and might not reflect patients’ perception of change.Attrition bias for the ‘hospital period’ might result from ICU death or transfers to other hospitals limiting generalisability.

## Background

 Survival after a prolonged critical illness has improved,^1 2^ but survivors frequently report poor physical, cognitive, mental and/or social health.^3^,^7^ This condition, termed post intensive care syndrome,^8^ might be driven by muscle loss and weakness^9^ whereby patients lose an average of 14% muscle mass within the first week of an intensive care unit (ICU) admission.^10^ ICU-acquired weakness (ICUAW) is associated with weaning failure, increased mortality and healthcare costs,^11^ as well as persisting physical impairments up to 5 years.^12 13^ Early mobilisation might improve survivors’ health.^14 15^ However, most studies are underpowered, single-centre and at risk of bias, lacking valid and responsive measurement instruments^16 17^ or detailed intervention-reporting such as the frequency, intensity, type or timing of activity achieved.^18^ Moreover, the largest trial to date found a signal of harm with high-intensity exercise, particularly in patients with diabetes.^19 20^ A responsive measurement tool for critically ill patients at risk of ICUAW is urgently needed to ensure reliable and robust results from early mobilisation trials.

The Chelsea Critical Care Physical Assessment tool (CPAx) has strong measurement properties for critically ill patients’ physical function and activity.^21^ It is a 10-item tool—rated on a 6-point Guttman scale—that includes the hallmark features of ICUAW, including respiratory function, cough, functional mobility and muscle strength.^22 23^ The CPAx score ranges from 0 (completely dependent) to 50 (independent in the measured constructs) without major floor and ceiling effects at ICU baseline to ICU and hospital discharge.^24^ The tool was predictive of the discharge destination, return to home and back to work in small, single-centre studies.^22 25 26^ Trained clinicians can score the CPAx in 5 min based on a standard physiotherapy session, or retrospectively from medical records if appropriate information is reported.^27 28^ Thereby, the burden for this vulnerable patient population is kept low. However, despite the increased use of the CPAx across the world,^29^,^32^ responsiveness has only been evaluated in small and selective samples.^2933^,^35^ Moreover, the minimal clinically important difference (MCID), relevant for sample size calculation, has not yet been established for critically ill patients at risk of ICUAW. This limits the usability of the CPAx in future clinical trials and the evaluation of patients’ progress in clinical practice. Rigorous investigation of responsiveness and the MCID of the CPAx is therefore urgently required. Additionally, it would be useful to investigate the predictive validity in a larger, international sample.

## Methods and analysis

### Objectives

This study, with an international population of critically ill adults with a prolonged ICU stay, aims to

Investigate the responsiveness of the CPAx, that is, its ability to detect change over time, from ICU baseline (study inclusion) to ICU discharge (‘ICU period’: primary outcome) and from ICU to hospital discharge (‘hospital period’: secondary outcome).Establish the MCID of the CPAx for the ‘ICU and hospital period’.Assess the predictive validity of the CPAx score at ICU baseline for the duration of mechanical ventilation and ICU length of stay, and at ICU discharge for the hospital discharge destination.

### Design

This prospective, international, multicentre, observational, longitudinal cohort study will be performed in accordance with the Declaration of Helsinki and Good Clinical Practice guidelines. The methodology is based on the COnsensus-based Standards for the selection of health Measurement INstruments (COSMIN) guideline^36^ and the protocol written according to the Strengthening the Reporting of Observational Studies in Epidemiology statement.^37^ An international, multicentre trial with a large sample of the target population across continents is required for the urgently needed outcome measurement to perform rigorous clinical trials in this field.

### Setting

This study will be conducted in two tertiary hospitals in Melbourne, Australia (Alfred Health, Monash Health) and one university hospital in Bern, Switzerland (Inselspital). Together, these hospitals include the full range of critical illness, including medical, surgical, trauma and burn units. The CPAx is routinely evaluated in clinical practice in Switzerland.^24 28^ Physiotherapists in Australian hospitals receive in-person CPAx training from the primary investigator^28^ prior to the start of the study to ensure reliability between centres.

### Participants

The target population for future clinical trials is critically ill patients with an increased risk for a prolonged ICU stay and ICUAW.^17^ Accordingly, adults (aged 18 years or older) with an acute critical illness of any origin who are receiving mechanical ventilation for at least 72 hours, who are seen by a physiotherapist and who are expected to remain in the ICU for a further 48 hours are eligible for study inclusion. This ensures a sufficient timeframe to detect a real change in physical function and activity. Exclusion criteria are imminent death (not expected to survive to hospital discharge), second or subsequent ICU admission for this hospital admission, transfer from an external ICU (with ICU stay of >72 hours) or a primary neurological diagnosis at ICU admission (ie, of the central nervous system including stroke, intracerebral haemorrhage, traumatic brain injury, spinal cord injury) as the CPAx is not validated in this cohort. We will further exclude patients who have a known pregnancy, those who lived in a care facility before their ICU admission (ie, with severe pre-existing mental or physical disability) or patients who need to be excluded by local ethical regulations.

### Procedures

There are no interventions in this observational study. Treating ICU physiotherapists at each site will screen potential participants during their daily clinical practice from Monday to Friday, maintaining a secure local log for all patients screened with reasons for study exclusion. Consent procedures follow local ethical requirements ranging from a waiver of consent to written informed consent.

Physiotherapy in the ICU is safe.^38^ Consequently, physiotherapy is routinely provided to all critically ill patients at the three participating sites. The chosen outcome measurements (table 1)^2239^,^43^ provide minimal burden for patients as they are based on routine physiotherapy interventions and can be scored even if mobilisation may be contraindicated. As such, physiotherapists complete the measurements as part of routine treatment, with documentation in the electronic health record. In case a patient is being discharged on a weekend (and not seen by a physiotherapist), the closest measurement to their discharge is recorded. Additionally, a global rating of change (GRC) scale for the ‘ICU and hospital period’ will be assessed by the treating physiotherapist.

**Table 1 T1:** Outcome measurements and data collection schedule

Outcome measurement	Description	Source data	ICU baseline*	ICU discharge†	Hospital discharge‡
Chelsea Critical Care Physical Assessment tool (CPAx)^22^	Physical function and activity rated on 10 items from 0 to 5 with a maximal score of 50 indicating independence	Routine physiotherapy	x	x	x
Global rating of change (GRC) scale^39^	Physiotherapists rating on patients’ change for ‘physical function and activity’ using a seven-point scale: ‘(1) very much improved; (2) much improved; (3) little improved; (4) no change; (5) little deterioration; (6) much deterioration; (7) very much deterioration’	Treating physiotherapist		x ‘ICU period'	x ‘hospital period’
ICU Mobility Scale (IMS)^40^	Mobility level on a scale from 0 (nothing) to 10 (walking independently)	Routine physiotherapy	x	x	x
Medical Research Council Sum Score (MRC-SS)^41^	Muscle strength in major muscles of the upper and lower limbs with a maximal summed score of 60 (full strength), less than 48 points indicates ICUAW	Routine physiotherapy (observation if unable to follow commands)	x	x	x
Richmond Agitation-Sedation Scale (RASS)^42^	Level of sedation and/or cooperation with 0 meaning alert and calm, +4 combative and −5 unarousable	Medical records	x	x	x
Modified Iowa Level of Assistance Scale (mILOA)^43^	Required assistance in functional task for six items rated from 0 (independent) to 6 (not testable)	Routine physiotherapy	x	x	x
Demographic, diagnostic, discharge data	Includes age, gender, body mass index, Acute Physiology and Chronic Health Evaluation (APACHE) II, age-adjusted Charlson Comorbidity Index (CCI), admission diagnosis, length of mechanical ventilation, ICU and hospital length of stay, mortality and discharge destinations	Medical records	x	x	x

* Within 72–144 hours after ICU admission.

† Within 24 hours before or after ICU discharge.

‡ Before hospital discharge.

ICU, intensive care unit; ICUAW, intensive care unit-acquired weekness.

### Responsiveness

Responsiveness is defined as the ‘ability to detect change over time’ and is considered an aspect of validity by the COSMIN guideline.^44^ Accordingly, criterion validity of CPAx change scores will be investigated with the GRC as a gold standard to distinguish patients with change (GRC 1–3) from those unchanged or deteriorated (GRC 4–7). These definitions are based on the clinical rationale that patients are at their lowest level of physical function and activity during the need for invasive mechanical ventilation (ICU baseline). No change or deterioration at ICU discharge is therefore equivalent to continued invasive life support or death, justifying their combination as an undesirable outcome. Patients who die will therefore be allocated the worst possible CPAx score of 0 indicating their inability to survive without invasive life support. In addition, construct validity will be explored using prospective hypotheses for each period about the expected magnitude of change as well as the expected correlation for change-scores between the CPAx and the other outcome measurements. The hypotheses are based on a previously published conceptual model^24^ reflecting on the overlapping constructs of the CPAx with the other measurement instruments and considering potential floor and ceiling effects for each period. Table 2 lists prospective hypotheses as well as the statistical methods for analysis.

**Table 2 T2:** A priori hypotheses for the expected magnitude of change scores (construct validity)

	Measured constructs	Hypotheses ‘ICU period’	Hypotheses ‘hospital period’
CPAx	Movement, function of muscles and respiratory system, mobility	Effect size >0.8 (calculated as mean change/SD average)	Effect size >0.8 (calculated as mean change/SD average)
IMS	Level of mobility	Positive, high correlation between CPAx and IMS (r>0.7)	Positive, moderate to high correlation between CPAx and IMS (r>0.6)
MRC-SS	Muscle function: used as reference standard for ICUAW (MRC-SS<48)	Positive, moderate to high correlation between CPAx and MRC-SS (r>0.6)	Positive, moderate correlation between CPAx and MRC-SS (r=0.4–0.7)
mILOA	Movement and mobility	Negative, moderate to high correlation between CPAx and mILOA (r>−0.6)	Negative, moderate to high correlation between CPAx and mILOA (r>−0.6)

CPAx, Chelsea Critical Care Physical Assessment tool; ICU, intensive care unit; ICUAW, intensive care unit-acquired weekness; IMS, ICU Mobility Scale; mILOA, Modified Iowa Level of Assistance Scale; MRC-SS, Medical Research Council Sum Score; r, Spearman’s rank correlation coefficient.

### Minimal clinically important difference

The MCID corresponds to the smallest, clinically meaningful change over time—a particularly relevant criterion to interpret efficacy of treatments.^44^ Despite a lack of consensus, the COSMIN guideline recommends using anchor-based approaches with a GRC over distribution-based methods that commonly rely on measurement error or heterogeneity of a population.^44^ A new systematic approach has been proposed to triangulate the MCID from anchor-based methods by using a range of distribution-based indicators.^45^ This approach has the advantage of considering clinical importance, the magnitude of the change and the variability of the measurement focusing on improvement as is appropriate for our population. Finally, we will determine the robust clinically important difference (RCID)^45^ to account for potentially major changes between the ‘ICU and hospital periods’. To this end, major change is defined as GRC 1–2 and minimal change as GRC 3.

### Predictive validity

Hypotheses testing will be used to confirm earlier research about the predictive validity of the CPAx, including the exploration of sensitivity and specificity for a return home after hospital discharge.^25^ The following hypotheses are tested:

The CPAx score at ICU baseline will negatively correlate with the duration of mechanical ventilation and the ICU length of stay (low to moderate correlation of −0.3 to −0.6).The CPAx at ICU discharge increases in a ranked order for three hospital discharge destinations (undesirable (ie, death or external transfer)≤in-patient rehabilitation≤home).

### Data management

Project data will be handled with the utmost discretion and only accessible to authorised personnel who require the data to fulfil their duties within the scope of their clinical practice and/or this research project. To protect all data from unauthorised or accidental disclosure, from alteration, deletion, copying and theft, paper-based data collection forms will be secured in a locked facility approved by the participating institution and/or electronic-based data collection in password-protected local area network computer drives supported by institution’s information technology services. To this end, all local project leaders will be trained in data controlling and entry. Ultimately, solely non-identifiable original study data will be collected and managed with Research Electronic Data Capture (REDCap) tools hosted and managed by Helix (Monash University, Australia).^46^ REDCap is a secure, web-based application designed to support data capture for research studies, providing (1) an intuitive interface for validated data entry; (2) audit trails for tracking data manipulation and export procedures; (3) automated export procedures for seamless data downloads to common statistical packages and (4) procedures for importing data from external sources.^46^

The analyses will be conducted with IBM SPSS Statistics (V.29) with a set two-sided α of 0.05 without any adjustments for multiple testing. Participants with missing outcome data will be analysed based on their availability for each period (pairwise exclusion). There will be no imputation of missing data.

### Sample size calculation

The COSMIN guideline recommends a sample size between 30 and 50 patients in the smallest group to investigate responsiveness via criterion validity.^49^ Based on our previous data,^24^ we expect the smallest group to be the ‘unchanged’ group, whereby approximately 26% of patients will not change when assuming a change of 6 points to be clinically relevant,^33^ yielding a sample size of n=115.

Solely considering survivors with an expected lack of change in 16%, we calculated that a sample of 97 survivors is required to demonstrate an AUROC of 0.8 (null hypothesis 0.6) with a power of 0.8 and an α of 0.05 (MedCalc on 26 December 2022). This is in line with the recommendation of ≥100 participants for a construct validity approach.^49^ We therefore aimed to include 120 participants (40 per centre). Based on our previous research,^24^ we do not expect any major missing data as all data are routinely documented at each site.

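### The 97 survivors in the AUROC power calculation do not follow from the stated 16% unchanged; the standard method gives about 87 to 88, and the error is conservative

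*Protocol article*

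**What the plan says.** The protocol article, Sample size calculation, contains one power statement. It is restricted to survivors ("Solely considering survivors with an expected lack of change in 16" per cent) and concludes that "a sample of 97 survivors is required to demonstrate an AUROC of 0.8 (null hypothesis 0.6) with a power of 0.8". The significance level is given in the words "with a power of 0.8 and an α of 0.05", and the source as "MedCalc on 26 December 2022". The Statistical analysis section makes the test two-sided ("with a set two-sided α of 0.05 without any adjustments for multiple testing"). The Responsiveness section sets the direction of the comparison: the global rating of change is used to "to distinguish patients with change (GRC 1–3) from those unchanged or deteriorated (GRC 4–7").

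The sample size section also says that about 26% of all patients are expected not to change, derives n=115 from a guideline minimum for the smallest group, cites a recommendation of at least 100 for construct validity, and settles on 120 participants.

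**The concern.** All the numerical inputs for a one-sample AUROC calculation are printed next to the answer, so the answer can be checked, and it does not come out. The value 97 appears if the percentage unchanged is typed in where the ratio of unchanged to changed patients belongs. A 16% share is a ratio of 0.19, not 0.16.

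This is the protocol's only statement of power, and readers will use it to judge the survivors-only AUROC, which corresponds to the planned sensitivity analysis without deaths. As printed, the number of survivors and the unchanged share probably belong to two different scenarios.

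**Working it through.** **Inputs.** AUROC 0.8 against a null of 0.6, power 0.8, α 0.05 and 16% of survivors unchanged (Sample size calculation); two-sided α (Statistical analysis); change, GRC 1–3, as the positive state (Responsiveness). The variance method is not stated. I assume Hanley-McNeil, the standard choice for a single AUROC.

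**Formula.** Let k = unchanged/changed, R1 = A/(2−A) and R2 = 2A²/(1+A). The large-sample variance multiplied by the number changed is

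V(A) = (R1 − A²)/k + (R2 − A²).

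The number changed is n = (1.96·√V(0.6) + 0.8416·√V(0.8))² / 0.2², and the number unchanged is k·n.

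- At A = 0.6: R1 − A² = 0.0686 and R2 − A² = 0.0900.
- At A = 0.8: R1 − A² = 0.0267 and R2 − A² = 0.0711.

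**Reproducing 97: k = 0.16.**
- V(0.6) = 0.0686/0.16 + 0.0900 = 0.5186, square root 0.7201.
- V(0.8) = 0.0267/0.16 + 0.0711 = 0.2378, square root 0.4876.
- n = (1.4114 + 0.4104)²/0.04 = 82.97 changed, and 0.16 × 82.97 = 13.28 unchanged.
- Rounding each group up: 83 + 14 = 97. The unchanged share is 0.16/1.16 = 13.8%.

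**Using the stated share: k = 16/84 = 0.1905.**
- V(0.6) = 0.3600 + 0.0900 = 0.4500, square root 0.6708.
- V(0.8) = 0.1400 + 0.0711 = 0.2111, square root 0.4595.
- n = (1.3148 + 0.3867)²/0.04 = 72.38 changed, and 13.79 unchanged.
- Rounding each group up: 73 + 14 = 87. The finite-sample form of the variance gives 88.

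**Power at 97 survivors with 16% unchanged** (0.16 × 97 = 15.5, so 81 changed and 16 unchanged).
- Null SE = √(0.0686/16 + 0.0900/81) = 0.0735. Alternative SE = √(0.0267/16 + 0.0711/81) = 0.0504.
- Power = Φ((0.2 − 1.96 × 0.0735)/0.0504) = about 87% (86% with the finite-sample variance).

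**Survivors expected among 120.** Deaths count as unchanged, so with death proportion d, 0.26 = d + 0.16(1 − d). Then d = 0.10/0.84 = 11.9%, and 120 × 0.881 = about 106 survivors, of whom 0.16 × 106 = 17 are unchanged and 89 changed. The same power formula gives a null SE of 0.0710, an alternative SE of 0.0487 and power of about 89%.

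**Other routes towards 97 at a true 16% share.**

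| Route | Survivors | Departure from the text |
|---|---|---|
| Null variance taken at AUROC 0.5 | 96.6 (97, or 98 rounding each group up) | Null is stated as 0.6 |
| Alternative variance only, unchanged as positive | 94 to 95 | Reverses the Responsiveness section and ignores the null variance |
| Binormal variance, change as positive | 99.1 (100 rounded up) | None, but does not give 97 |

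**The case against.** The best defence is that the article names the software but neither the variance formula nor the ratio entered, and an article may leave such detail to the full protocol. The mismatch of 87 with 97 is then a mismatch under an assumed method. A binormal variance gives 100, which is closer to 97 than 87 is, and taking the null variance at 0.5 lands on 97 or 98. This stands as far as the cause is concerned: entering 0.16 as the ratio is an inference. It does not rescue the printed figure. Of the routes tried, only the 0.16 ratio gives exactly 97 with the other stated inputs unchanged; the null-at-0.5 route needs a null other than the one stated. The point is also not about omitted detail, since a figure and its inputs are both printed and disagree.

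It is also fair that 97 is not shown to drive recruitment. The n=115 and the minimum of 100 are separate bases, both above 97, and 120 clears both.

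A reader might go further and infer that the study is underpowered. If the unchanged patients are coded as positive, the Hanley-McNeil formula asks for 117 survivors, and power falls to about 73% at 97 survivors and 76% at 106. The document does not support that reading. The Responsiveness section treats change as the state to be detected. Moreover, the true AUROC does not depend on which group is called positive: the gap between 87 and 117 reflects the distributional approximation in the formula, and under the binormal variance it is only 100 against 112.

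**Conclusion.** The point holds as an error in a stated figure. Under the Hanley-McNeil variance, with two-sided α and change as the positive state, 97 is about 10 survivors more than 16% unchanged requires. The probable explanation is that 0.16 was entered as the ratio, but only the original software entry can confirm it.

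The consequence is limited. In the protocol's own orientation the slip is conservative, with power of about 87% at 97 survivors and about 89% at about 106. The last figure assumes that the 26% and 16% describe the same cohort and that all deaths are counted as unchanged. No shortfall in power is shown, and no decision on design or conduct depends on the correction. It is still worth making, because this is the only power statement in the document.

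**What to change.** Check the original software entry and correct whichever of 97 or 16% is wrong. If 16% stands, with change as the positive state and the Hanley-McNeil variance, the requirement is about 87 to 88 survivors. If 0.16 was the intended ratio, the unchanged share should read 13.8% and 97 can stay. State the group ratio, the positive state and the variance method beside the figure, and add the power at the roughly 106 survivors expected from 120 patients (about 89% under the same assumptions).

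The cost is one or two sentences. Recruitment stays at 120, and data collection and analysis are unaffected.
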